## Abstract

**Background:**

With an increasing proportion of older adults and the associated risk of Alzheimer’s Disease and Related Dementias (ADRD) around the globe, there is an urgent need to engage in ADRD risk reduction efforts. African American (AA) older adults in the U.S. are disproportionally impacted by ADRD compared to other races and ethnicities. Mindful walking integrates two potentially protective factors of ADRD by elevating mindfulness and physical activity (i.e., walking), resulting in a synergistic behavioral strategy that is feasible and safe for older adults. However, the efficacy of applying this intervention for cognitive health outcomes has not been evaluated using experimental designs.

**Methods:**

This paper documents the goal and protocol of a community-based, mindful walking randomized controlled trial to examine the short- and longer-term efficacy on cognitive and other health-related outcomes in ADRD at-risk AA older adults. The study outcomes include various brain health determinants, including cognitive function, quality of life, psychological well-being, physical activity, mindfulness, sleep, and overall health status. In addition, the estimated costs of program implementation are also collected throughout the study period. This study will recruit 114 older adults (ages 60+ years) with elevated ADRD risk from the Midlands region of South Carolina. Older adults are randomly assigned to participate in 24 sessions of outdoor mindful walking over three months or a delayed mindful walking group (*n*=57 in each group). Participants in both groups follow identical measurement protocols at baseline, after 12 weeks, after 18 weeks, and after 24 weeks from baseline. The outcome measures are administered in the lab and in everyday settings. Costs per participant are calculated using micro-costing methods. The eliciting participant costs for mindful walking engagement with expected results are reported using the payer and the societal perspectives.

**Discussion:**

This study will generate evidence regarding the efficacy of mindful walking on sustaining cognitive health in vulnerable older adults. The results can inform future large-scale effectiveness trials to support our study findings. If successful, this mindful walking program can be scaled up as a low-cost and viable lifestyle strategy to promote healthy cognitive aging in diverse older adult populations, including those at greatest risk.

**Trial registration:**

ClinicalTrials.gov number NCT06085196 (retrospectively registered on 10/08/2023).

**Supplementary Information:**

The online version contains supplementary material available at 10.1186/s12877-024-05090-2.

## Background

Alzheimer’s disease and related dementias (ADRD) have become one of the leading causes of death and disability [1–3]. There is currently no effective treatment to cure ADRD. Over six million Americans and one in every nine older adults are currently living with ADRD, and the projected total ADRD-related health costs will rise to one trillion a year by 2050 [4]. Among individuals living with ADRD, African Americans (AA) are over-represented compared to other race and ethnicity groups [5]. AA older adults (ages 65+) have the highest ADRD prevalence rate (~ 14%) compared to other racial and ethnic groups [6, 7]. Thus, ADRD has placed a tremendous economic burden on AA and their families, who bear 33% of total ADRD costs nationally [8]. Additionally, as new pharmacological treatments become available, there is concern that AAs, among other populations, may not be able to afford the cost [9]. Most ADRD prevention programs to date are overwhelmingly conducted with non-Hispanic White individuals, limiting our understanding of preventing ADRD in the AA population [10, 11]. This study commits to sustaining cognitive health among AA older adults by developing and implementing a mindful walking intervention to serve this priority population urgently requiring preventive strategies to reduce ADRD risk.

The Advisory Council on Alzheimer’s Research, Care, and Services and the Physical Activity Guidelines Advisory Committee identified physical activity (especially moderate-to-high intensity) as a major protective factor for brain health [12, 13]. Existing older adult physical activity programs usually require moderate-to-high mobility levels to enter the programs [14–16]. However, approximately 28% of older adults have mobility barriers, limiting their ability to exercise at the recommended intensity levels to reap the benefits [17]. Older adults with higher ADRD risk also experience more physical barriers or mobility limitations [18], making them likely to fail inclusion criteria for exercise programs or preventive clinical trials. This study focuses on a relatively achievable physical activity type (walking) with the incorporation of mindfulness practice to sustain brain health in ADRD at-risk older AAs.

Research suggests that accruing physical activity at a lower intensity, such as walking, may improve cognition and related brain structures in older adults [19–21]. Walking is an ideal intervention target as it is the primary daily activity and the most familiar physical activity type among older adults [22]. It is also considered safe and appealing to most older adults [23–25]. Several older adult walking programs have been successfully applied in shopping malls [16, 26]. However, these mall walking programs are usually restricted to the non-business time windows for walkers, and the group walking setting provides less flexibility for older adults who may not meet the group walking schedule. The current mindful walking program is implemented in an open space accessible at any time for older adults in the community. It also does not require a walking group or walking partners, which mitigates one of the barriers for older adults with limited social networks or who prefer to engage in physical activity alone [23]. Moreover, there is evidence to suggest that outdoor walking or physical activity confers more health benefits than indoor walking [27, 28].

When walking at a slower pace, it is easy to incorporate mindfulness practice, which is another promising strategy for sustaining brain health in older adults [29–32]. Available literature suggests that mindfulness programs appeal to older adults, as indicated by the high program compliance and completion rates [29]. Mindfulness practice cultivates individuals’ attention and awareness in every present moment and engages individuals’ present-moment experience in a non-judgmental manner [33, 34]. While existing mindfulness-based interventions primarily focus on mental health outcomes (e.g., stress reduction) [35–37], the neurobiological mechanisms underlying mindfulness practice are also closely linked to cognitive ability [38–40]. When practicing mindfulness, various brain regions that are linked to sustained attention and executive function are stimulated (e.g., anterior cingulate cortex, autonomic nervous system) [31, 32, 38, 41, 42]. Based on the findings that walking and mindfulness practice are both promising strategies to sustain cognitive function and well-being in older adults, combining both strategies may yield a synergy to benefit brain health [43–45].

Our recent work suggests that short bouts of mindful walking sessions are feasible and safe to implement in the community and may elevate older adults’ cognitive function in the short term [46, 47]. However, the intervention efficacy of mindful walking on sustaining cognition has not been tested using an experimental approach, especially among ADRD at-risk older populations. Therefore, this study is designed to narrow the literature gap using a randomized controlled trial (RCT) to examine the potential cognitive benefits generated from mindful walking engagement.

## The current study

The primary goal of this study is to evaluate the short- and longer-term effects of mindful walking intervention on cognitive health outcomes in AA older adults at risk for ADRD. This mindful walking program partners with local organizations, federal agencies, and stakeholders to recruit and retain participants from our priority population. Our team administers lab- and device-based measures on multiple occasions to evaluate the intervention effect across 24 weeks. In addition, this study estimates the total cost of planning and implementing the current mindful walking program. Finally, we evaluated program recruitment and retention for future large-scale implementation studies. The Institutional Review Board approved the study protocol and all materials described in this paper (Pro00123487).

## Methods

This study is a two-arm, randomized controlled trial (RCT) comparing an outdoor mindful walking intervention versus a delayed intervention comparator. Figure 1 depicts the study design and measurements throughout the trial. This program is implemented in South Carolina (SC), which has a pronounced ADRD race disparity. Based on the SC ADRD registry, AAs comprise 27% of the SC residents diagnosed with ADRD. In addition, older SC AA residents (ages 65+) are 35% more likely to have ADRD compared to non-Hispanic White older adults living in SC [48]. This mindful walking study took place at the South Carolina State House outdoor walking trail located in downtown Columbia.

**Fig. 1 Fig1:**
[figure not shown]
Overview of study design

Older adults’ cognitive function is the primary study outcome in this study. The secondary outcomes are quality of life, overall health status, perceived stress, depressive symptoms, physical activity (steps), sleep, and mindfulness. The short-term effect refers to any differences in the primary and secondary outcomes from baseline to post intervention (after the 12 weeks) between the two groups. The longer-term effect refers to differences in the primary and secondary outcomes between baseline and 18 weeks as well as 24 weeks between the two groups. More detailed descriptions in the primary and secondary study outcomes are provided in the Measures section. We hypothesize that the short-term and the longer-term differences of the primary and secondary outcomes can be observed between the two groups after the intervention period.

### Participants

This study will recruit a total of 114 gender-inclusive older AA adults aged 60 and above in the Midlands region of SC. Instead of using the typical age 65 cutoff for older adults, the age of 60 is selected because this study is designed to inform risk-reductive behavioral strategies to sustain cognitive health during the early preclinical stage of ADRD. Our inclusion and exclusion criteria, as outlined below, also seek to make this program available to most AA older adults who have increased risks for developing ADRD (e.g., does not require prominent levels of physical capacity and mobility), and thus, may benefit from participating in mindful walking.

The inclusion criteria included: (1) African American older adults age 60 and above, (2) have at least one ADRD risk factor (including experiencing subjective cognitive decline or memory complaints, having a family history of ADRD, being physically inactive at enrollment based on the 2018 Physical Activity Guidelines for Americans, having higher BMI (≥ 25)), (3) have adequate hearing and visual ability to complete study tasks and assessments, (4) English proficiency, (5) be medically stable with or without medication, (6) be able to provide informed consent, and (7) be willing to be randomized to one of the two groups. The exclusion criteria included: (1) have a clinical diagnosis of ADRD or other brain abnormalities (e.g., strokes, epilepsy, Parkinson’s disease), (2) have a clinical diagnosis of a psychiatric disorder (i.e., major depression, post-traumatic stress disorder, bipolar disorder), (3) unable to walk independently (i.e., need caregiver’s assist), (4) plan to have surgery or relocate outside the area within the next 12 months, and (5) currently participate in other study involving physical activity, mindfulness or meditation, or cognitive training. We selected these exclusion criteria to ensure that older adults have the capacity to carry out the study protocol and that their current health condition will not bias or interfere with the study outcomes.

### Recruitment

This study engaged with community partners who share the same mission to promote healthy aging and address ADRD in older populations (e.g., SC AARP, SC Alzheimer’s Association Chapter, SC Department on Aging). These local partners have rich experience interacting with underrepresented racial and ethnic groups, so they are assisting in recruiting our priority population of AA participants. They also serve on our community advisory board (CAB) to provide insights and feedback on the planning, outreach, recruitment, and implementation of the mindful walking program.

In addition to the community-engaged recruitment approach, we also leverage the SC Alzheimer’s Disease Registry, the Dementia Dialogues® Certified Instructors in SC, and the Office for the Study of Aging’s (OSA) listserv, all hosted by the OSA at the University of South Carolina. The ADRD registry is the most comprehensive database among the only three population-based registries in the US [48]. Our study does not recruit older adults with cognitive impairment, but this unique platform can help us identify eligible AA older adults by sending out promotional materials/mailers to the homes of individuals with ADRD to inform eligible family members and caregivers. Normally, the family members or caregiver(s) of the care recipient in the ADRD registry monitor the mails and they likely meet the inclusion criteria to participate in this study. Other general recruitment methods are also carried out by the research team, including distributing fliers and mailers at community events, senior living facilities, local churches, and retirement centers. We also send out electronic flyers to relevant email listservs, online forums/support groups, and paid public service announcements. The study recruitment has occurred on a rolling basis and will continue until May 2024.

#### Screening and First Lab visit

Potential participants are contacted by the study staff to complete a phone screening to determine their eligibility based on the inclusion/exclusion criteria. Eligible older adults who pass the screening are invited for the first in-person baseline lab visit. During this lab visit (Week 0), a trained staff provides a brief study description to participants and obtains their informed consent. After giving consent, participants are guided to complete anthropometric and baseline measures regarding their demographics, mental and physical health status, and other individual characteristics (see Measures section). Lastly, the staff demonstrates to the participants how to wear the activity monitor and completing smartphone tasks that will be performed throughout the study period. After the demonstration, participants practice the tasks on the smartphone and wear the activity monitor to ensure they feel comfortable using these technologies. When participants exit the first visit, they receive a study handbook that includes detailed instructions regarding the study protocols and study contact information.

#### Randomization

After completing the baseline measures, participants are randomly assigned to the mindful walking group, or the delayed mindful walking group based on block randomization by the staff. Random blocks were generated by a methodologist on the team, stratified by sex (male vs. female) and baseline cognitive function (normal cognition vs. mild cognitive decline based on MoCA; see Measures section) to balance the two groups. The rest of the research team is blinded to the condition allocation sequence kept in sealed envelopes. Participants assigned to the intervention group schedule their 24 mindful walking sessions with the staff from week 1 to week 12. Participants assigned to the delayed mindful walking group are asked to live their normal lives and follow their regular daily routines without changing their behaviors until they start their mindful walking sessions after week 24. The measurement schedule is identical between the two groups from baseline to the last follow-up to compare group differences with or without the intervention.

#### Outdoor mindful walking sessions

The mindful walking group participated in 24 sessions of outdoor mindful walking supervised by trained research staff over 12 weeks. Participants schedule two walking sessions on two different days per week, with at least one day apart between two consecutive sessions. Each session involves 30 min of individual walking along a flat, designated oval walking trail (~ 0.4 miles for one lap) in a green space surrounding the South Carolina State House. The mindful walking program is designed as an individual activity to facilitate the elevation of a mindfulness state without distraction from social interactions.

On every scheduled mindful walking day, participants meet with the staff at the walking site between 8 am and 6 pm. The research staff greet participants and instruct them on the specific mindful walking skill for that day’s walking through a brief demonstration. During participants’ mindful walking, the staff provides supervision from a short distance (around the central spot of the oval walking trail) and monitors their walking time. Each participant also completes a brief survey on a smartphone right before and after their 30-minute walk. Lastly, the staff conducts a brief interview after participants finish the post-walking survey to understand their experiences during mindful walking. Participants are encouraged to select their most relaxing and comfortable way of walking at a relatively slower pace compared to their typical walking. Walking at a slower and more comfortable speed can help elicit a state of mindfulness and elevate their awareness of present-moment experiences [49], which is a critical component of our intervention. Walking sessions can be rescheduled with participants in case of adverse weather conditions (e.g., storms, heavy rain, hot temperatures) or unexpected incidents (e.g., family emergency).

Across the 24 sessions, the trained research staff instruct participants to practice three fundamental mindful walking skills. These skills involve being aware and attentive to the rhythm of their breathing, being aware and attentive to the movement of each step, and mentally scanning the whole body top-down and bottom-up to identify and accept sensations or feelings that arise in every present moment [33, 50]. These three basic mindful walking skills are introduced and conducted progressively as the walking sessions proceed (see mindful walking session design in Table 1). While various mindfulness skills currently exist in interventions to promote health, we focused on these fundamental mindfulness practices because they are easy for the general population to follow without any prior experience. Thus, this program can enhance participant reach and acceptability.

**Table 1 Tab1:** Components of the 24 mindful walking sessions

Walking Session	1	2	3–4	5–6	7–8	9–10	11–12	13–14	15–16	17–18	19–20	21–22	23–24
Practice Mindful skill 1	-	X	X	X	-	-	X	X	-	-	X	X	X
Practice Mindful skill 2	-	-	-	-	X	X	X	X	-	-	X	X	X
Practice Mindful skill 3	-	-	-	-	-	-	-	-	X	X	X	X	X

Note: Each walking session lasts for 30 min. Mindfulness skill 1: practice walking while sustaining attention to the rhythm of every breath. Mindfulness skill 2: practice awareness of the gentle heel-to-toe rhythm for each step. Mindfulness skill 3: practice doing a mental body scan to expand attention to any bodily sensations or feelings that arise during walking. The first walking session does not involve mindful walking skill. It is designed to provide a quick introduction to the walking trail, familiarize participants with the walking route, and practice walking at a comfortable pace. The 23rd and 24th walking sessions overlap with the 14-day monitoring period of physical activity (using activPAL) and everyday cognition (using the M2C2 app)

#### Safety considerations

Our mindful walking intervention is considered safe for older adults because it only requires participants to perform a mental activity in addition to walking (i.e., a lifestyle behavior they engage in daily life). There were also no adverse events reported in our previous mindful walking feasibility study [46]. However, we implement extra measures and protocols to ensure participant safety during the intervention period. Prior to each walking session, the research staff conducts a safety check of the walking trail. When participants are walking, the staff observes them from a distance (within approximately 200 feet) to respond promptly to any incident. The research staff also makes weekly check-in phone calls to ask participants if they experienced any physical or psychological discomforts or adverse events relevant to mindful walking. In the event of any moderate or severe symptoms or the development of health conditions, the research team will obtain necessary information to determine the severity and relatedness to the intervention. If appropriate, the team will encourage participants to see a healthcare provider and will report the adverse event(s) to the IRB and the relevant agencies.

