### Adherence plan

Participants can decide to drop out of the study at any time without providing a reason, and there are no consequences if they quit the study. A variety of strategies are employed to promote intervention adherence, measurement completion, and study retention. The research team strives to establish a positive rapport with participants and provides responsive support throughout the study period. Prior to enrollment, the staff outlines the potential pros and cons of study participation to let participants make an informed decision about participating and the expectations [83]. The weekly check-in phone calls and text messages conducted during the intervention period also encourage participants to comply with the study protocol. The staff delivers reminder texts or emails to each participant for their upcoming walking sessions and lab visits. During the baseline lab visit, participants should identify two secondary contacts in case the study team can not reach the participant. We offer flexible scheduling to accommodate participants’ time for the walking sessions and visits, including walking on weekend days.

In addition, financial incentives are provided after participants complete the in-person measures and the activity monitoring. Participants receive up to $200 if they complete the entire study with proper compliance (complete all in-lab measures and provide ≥ 70% of the EMA and activPAL data). Specifically, they receive $25 for completing the baseline and the-12 week measures, $60 for completing the 14-day EMA monitoring, $35 for the 18-week measures, and $40 for the 24-week measures. Participants who complete the entire study protocol with ≥ 70% compliance rate are eligible to participate in a drawing to earn an extra $40. Lastly, participants will receive a summary of their physical activity levels during the monitoring period collected by the activPAL device.

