### Data preparation, analysis, and management

***Power and sample size consideration***. We conduct apriori power and sample size calculation to detect at least a small between-group effect (Cohen’s *d* = 0.2) based on the available literature showing the anticipated effect sizes from mindfulness-based physical activity programs and cognitive health in older adults [84–86]. The power analysis R package “powerlmm” is used to determine the sample size in the mixed-effects analysis framework with repeated measures. The package identified that a total sample size of 114 participants (57 in each group) would support the detection of the pre-specified small effect size between two groups with sufficient power (≥ 0.80) [87]. We plan for a 15% dropout rate based on the attrition rate in our preliminary study and the annual injury rates (~ 5%) in older adults (i.e., due to serious falls) that lead to unanticipated dropouts [88]. Thus, we will recruit 18 extra participants to account for the attrition, so the actual power for analysis is likely to be greater.

***Statistical analysis***. After the study is completed, we will first examine the distributions of all the quantitative outcome variables prior to any statistical analysis. If any variables violate the normal distribution assumption, we will apply proper sampling distributions and link functions to model the data [89]. We will apply the generalized linear mixed-effects modeling to examine the short- and longer-term effects of mindful walking on cognition and other study outcomes. The repeated measures collected across the study period are the within-subject components, and the group allocation (mindful walking vs. delayed walking group) is the between-subject component in the model. The primary interest in the model is the Time x Group interaction term, which will determine whether significant differences exist in the outcomes between the two groups from baseline to post-intervention. The analyses will be conducted in R program version 4.0.1 [90]. Participants’ baseline characteristics and demographics (e.g., sex, age, BMI, general health status, etc.) will be adjusted in all models. We will also control for participants’ enrollment time of the year (in months) in our analyses to account for any potential seasonal effects that may impact the study outcomes.

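### The weekly adverse-event question is limited to events relevant to mindful walking and to the intervention period, and no identical cause-neutral question to both arms through week 24 is described

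*Protocol article*

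**What the plan says.** The Safety considerations section gives both the route and the content of adverse-event questioning. Staff make weekly calls to ask participants "if they experienced any physical or psychological discomforts or adverse events relevant to mindful walking". The same section introduces its safeguards with "we implement extra measures and protocols to ensure participant safety during the intervention period", and the Adherence plan dates the calls in the same way: "weekly check-in phone calls and text messages conducted during the intervention period".

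The sentence after the call question is broader and gives the team the judgement of how serious an event is and whether it is related to the intervention. It begins: "In the event of any moderate or severe symptoms or the development of health conditions, the research team will obtain necessary information to determine the".

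Under Randomization, the delayed group keeps to its usual routine "without changing their behaviors until they start their mindful walking sessions after week 24". The measurement schedule is otherwise the same in both arms, with lab visits at baseline and at 12, 18 and 24 weeks. Table 2, which lists the measures and their timing, contains no adverse-event item.

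The sample-size paragraph expects injuries in this population. It bases its dropout allowance partly on "annual injury rates (~ 5%) in older adults", attributed to serious falls.

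**The concern.** Asking about events and judging their cause are separate steps, and the asking should come first and be neutral. Here the question as worded builds the causal judgement into the asking. A participant who falls at home, or whose knee worsens between sessions, and who sees no link to the walks has not been asked about it.

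The second difficulty is comparability. A weekly question about events relevant to mindful walking has content for someone who is walking and almost none for someone who will not start until after week 24. The intervention-period timing also leaves weeks 13 to 24 without any described active questioning in either arm, although follow-up for the outcomes continues.

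The abstract already calls the strategy feasible and safe for older adults, and the Discussion looks ahead to adoption by insurers and public agencies. The Discussion also says that people using a cane or walker are eligible. A statement about tolerability in this trial will be read in that light, and it should not rest on counts that depend on the participant's own attribution and have no matching count in controls.

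**Working it through.** **Plan's own figure.** The article states no adverse-event rate, no safety sample size and no safety comparison, so there is no figure to reproduce. The main check is of the text.

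**Routes by which an event could become known**

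| Route (section) | Who it reaches | When | Cause-neutral? |
|---|---|---|---|
| Weekly call (Safety considerations; Adherence plan) | Participants, arm not specified | Intervention period | No, worded by relevance to mindful walking |
| Staff observation and post-walk interview (Safety considerations; Outdoor mindful walking sessions) | Only people who are walking | Sessions, weeks 1 to 12 | Not limited by attribution, but absent in controls before week 24 |
| Assessment of moderate or severe symptoms or new conditions (Safety considerations) | Not specified | Not specified | Yes, but it governs what happens once an event is known and describes no way of finding it |
| Reasons for attrition, including medical (Evaluate program recruitment and retention) | Total sample | Weeks 12, 18 and 24 | Yes, but only for people who leave; the stated breakdowns are by demographics and recruitment source, not by arm |
| CES-D, PSS-10, SF-36, 10-meter walk (Table 2) | Both arms | Baseline, 12, 18, 24 weeks | Yes, but these are scores and do not count falls or injuries |
| Medications and comorbidities | Both arms | Each lab visit in the text; Table 2 lists medication use at baseline only | Does not record falls or injuries as events |

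No row is cause-neutral, counts events, covers both arms and runs to week 24.

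**Does the answer depend on whether controls are called?** If they are not, there is no solicited control count. If they are, the question as worded still asks them about an exposure they have not had. The two counts fail to match either way.

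**Scale.** Inputs: about 5% a year (sample-size paragraph) and 57 per group. Assumption: the rate applies evenly over time and equally in both arms.

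- Simple proportion, 24 weeks: 57 × 0.05 × 24/52 = 1.32 injuries per arm.
- Constant hazard, 24 weeks: p = 1 − 0.95^(24/52) = 0.0234; 57 × 0.0234 = 1.33. Chance of at least one in an arm: 1 − (1 − 0.0234)^57 = 74%.
- Constant hazard, 12 weeks: p = 1 − 0.95^(12/52) = 0.0118; 57 × 0.0118 = 0.67. Chance of at least one: 49%.
- With the 18 extra recruits, (114 + 18)/2 = 66 per arm: 66 × 0.0234 = 1.54 by week 24, and the chance of at least one is 79%.

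A small number of background injuries is therefore likely in each arm, and a walking-arm count cannot be read without a control count obtained in the same way.

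**What identical questioning could and could not show.** With 57 per arm, a control risk of 0.0234 and a two-sided Fisher exact test at 0.05, power is about 1.5% for a doubling of risk, 7% for a tripling and 18% for a fourfold risk. One injury against seven gives p = 0.06. Even perfect ascertainment supports only a descriptive table.

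**The case against.** The strongest reply is that this is a condensed article, that event forms and control-arm procedures usually sit in the full protocol, and that the article never says controls are not called. That stands against one tempting reading. A reader might infer that controls are asked about none of their injuries and that the trial will have no control-arm count at all. The article does not support this. The intervention period is a time window rather than an arm, and the Adherence plan speaks of participants generally. Silence on control-arm collection is not exclusion of it.

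A second tempting reading is that, among walkers, only events the participant links to walking will be captured. This fails too. Staff observe the walks and interview participants after them, and missed and partially completed sessions are logged. The follow-up sentence covers any moderate or severe symptom or new condition. The qualifier in the call question may also attach only to adverse events and not to discomforts.

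It is also fair to say that the roughly 5% rate concerns injuries that lead to dropout, so some of them would surface as medical reasons for attrition in either arm. Safety is not a named outcome, no between-arm safety comparison is promised, and one would have almost no power. A reader should not infer that the trial could otherwise have determined whether walking raises or lowers the injury rate.

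What the reply does not reach is the wording itself. The content of the question is stated, not left out, and it places the participant's attribution ahead of the team's. On any of the readings above, the adverse-event part of the question remains filtered, and no arm-neutral question is described.

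**Conclusion.** The point holds in limited form. As written, solicited adverse events are under-ascertained where the participant does not attribute them to walking, and the solicited counts are not comparable between arms whether or not controls are called. The other routes catch some events but do not combine into an arm-neutral count through week 24.

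The size is modest: about 1.3 expected injuries per arm by week 24 (1.5 with 66 per arm), assuming the plan's annual rate applies evenly and equally to both arms. That rate covers only serious injuries, so milder falls and symptoms would come on top, at a rate the article does not give. The gain from a change is unbiased and comparable reporting, not a test of safety. The change is worth making because it is cheap and the article reports recruitment as still ongoing. If the full protocol already puts a neutral question to both arms on one schedule, the remaining action is to align the call wording with it.

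**What to change.** 1. Remove the restriction to events relevant to mindful walking from the weekly call question, so that participants report any event and the team assigns relatedness afterwards, as the next sentence of the section already provides.
2. At the existing 12-, 18- and 24-week lab visits, put one identical open question to both arms: any fall, injury, new symptom or medical visit since the last visit, regardless of cause. Add it to Table 2.
3. Report the visit-elicited events by arm, descriptively. Show call-elicited and session-elicited events separately, because contact intensity differs between arms and pooling them would bring the imbalance back.
4. State how participants enrolled before the change are handled, since their earlier visits will lack the question.

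The cost is one question at three existing visits, a wording change in the call script and a little more event recording. No extra visits, calls or staff are needed, and controls receive no additional contact that could affect the outcome comparison.
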